# Levofloxacin versus placebo for the prevention of tuberculosis disease in child contacts of multidrug-resistant tuberculosis: study protocol for a phase III cluster randomised controlled trial (TB-CHAMP)

**DOI:** 10.1186/s13063-018-3070-0

**Published:** 2018-12-20

**Keywords:** Tuberculosis, TB, Resistant, Trial, Prevention, Randomised, MDR, Placebo, Child

## Abstract

**Background:**

Multidrug-resistant (MDR) tuberculosis (TB) presents a challenge for global TB control. Treating individuals with MDR-TB infection to prevent progression to disease could be an effective public health strategy. Young children are at high risk of developing TB disease following infection and are commonly infected by an adult in their household. Identifying young children with household exposure to MDR-TB and providing them with MDR-TB preventive therapy could reduce the risk of disease progression. To date, no trials of MDR-TB preventive therapy have been completed and World Health Organization guidelines suggest close observation with no active treatment.

**Methods:**

The tuberculosis child multidrug-resistant preventive therapy (TB-CHAMP) trial is a phase III cluster randomised placebo-controlled trial to assess the efficacy of levofloxacin in young child contacts of MDR-TB cases. The trial is taking place at three sites in South Africa where adults with MDR-TB are identified. If a child aged < 5 years lives in their household, we assess the adult index case, screen all household members for TB disease and evaluate any child aged < 5 years for trial eligibility. Eligible children are randomised by household to receive daily levofloxacin (15–20 mg/kg) or matching placebo for six months. Children are closely monitored for disease development, drug tolerability and adverse events. The primary endpoint is incident TB disease or TB death by one year after recruitment. We will enrol 1556 children from approximately 778 households with an average of two eligible children per household. Recruitment will run for 18–24 months with all children followed for 18 months after treatment. Qualitative and health economic evaluations are embedded in the trial.

**Discussion:**

If the TB-CHAMP trial demonstrates that levofloxacin is effective in preventing TB disease in young children who have been exposed to MDR-TB and that it is safe, well tolerated, acceptable and cost-effective, we would expect that that this intervention would rapidly transfer into policy.

**Trial registration:**

ISRCTN Registry, ISRCTN92634082. Registered on 31 March 2016.

**Electronic supplementary material:**

The online version of this article (10.1186/s13063-018-3070-0) contains supplementary material, which is available to authorized users.

## Background

Tuberculosis (TB) infection signifies that *Mycobacterium tuberculosis* (*M. tuberculosis*) is present in the body without causing symptoms, signs or radiological changes. TB disease, alternatively, is associated with symptoms, signs or radiological changes. Exposure to a person with TB disease can lead to infection with *M. tuberculosis*. Providing preventive therapy to exposed contacts is a viable strategy for reducing their risk of developing TB disease. This is especially so for young children and people living with HIV who, in the absence of appropriate preventive therapy, have a higher risk of disease progression following exposure to and infection with *M. tuberculosis* [1, 2].

The World Health Organization (WHO) estimated that 558,000 individuals developed multidrug-resistant (MDR) TB disease in globally in 2017 [3]. MDR-TB is defined as TB disease caused by *M. tuberculosis* resistant to rifampicin and isoniazid. With the rollout of rapid molecular diagnostic tools including Xpert MTB/RIF, the number of diagnosed adult MDR-TB cases is increasing, with associated increasing numbers of child contacts identified. Modelling suggests that two million children are currently living with MDR-TB infection [4] and of the children infected with *M. tuberculosis* who progress to disease, 90% will do so within 12 months [5]. While treatment outcomes for MDR-TB disease in children are considerably better than in adults [6, 7] the treatment is complex, long, poorly tolerated and associated with frequent and significant adverse events (AE), including ototoxicity, thyroid dysfunction, nausea and vomiting [6, 8–10]. Child-friendly formulations of second-line TB drugs are limited and MDR-TB disease is expensive to treat [11, 12] with prolonged hospitalisation being common for children. Prevention of MDR-TB disease in children is therefore of paramount importance. The United States Centers for Disease Control identified the need for a trial of MDR-TB preventive therapy in 1992 [13]. Since then numerous international agencies have also recommended that such a trial should be a global health priority [14–20] but none have been completed to date, despite the global increase in MDR-TB.

There is strong evidence for the efficacy of isoniazid to reduce the risk of progression to TB disease in child and adult contacts of people with drug-susceptible TB [21, 22]. Isoniazid monotherapy, given daily for six months, is therefore recommended by the WHO in children aged < 5 years and HIV-infected individuals, regardless of age, following exposure to infectious drug-susceptible TB [5, 21–24]. However, the WHO does not currently recommend any specific drug regimen for the contacts of people who are living with infectious MDR-TB. No randomised controlled trials have been completed to assess the efficacy of any regimen to prevent MDR-TB [25], but a recent systematic review and meta-analysis of multiple observational studies of MDR-TB preventive therapy concluded that although the results should be interpreted cautiously, a number of different regimens were associated with a reduction in the risk of subsequent TB disease and were cost-effective [26]. Our primary hypothesis is that levofloxacin, given daily for six months, will protect children exposed to MDR-TB from developing TB disease. We also hypothesise that this treatment will be well tolerated, safe and cost-effective.

## Methods

### Trial design

The tuberculosis child multidrug-resistant preventive therapy (TB-CHAMP) trial is a phase III cluster randomised placebo-controlled trial to assess the efficacy of levofloxacin to prevent TB disease in young (aged < 5 years) child contacts of people with MDR-TB disease.

### Rationale for trial design

#### Target population

This trial specifically targets child household contacts of MDR-TB cases aged < 5 years for two reasons. First, children aged < five years are at the highest risk of progressing to TB disease following infection [2]. Second, concordance of drug susceptibility test (DST) results is high between adults with MDR-TB and young child household contacts [27–29]. Young child household contacts are therefore most likely to benefit from MDR-TB preventive therapy. In addition, global policy and most national guidelines in high-burden settings recommend TB preventive therapy only for child contacts aged < 5 years or for children living with HIV, following exposure to a person with drug-susceptible TB [30]. Although children aged > 5 years, living with HIV, would likely benefit from preventive therapy, the potential for reduced concordance with the identified source case meant that the decision was made to restrict the trial to children aged < 5 years. Children aged < 5 years will be enrolled, regardless of tuberculin skin test (TST) or interferon-gamma release assay (IGRA) status. This is a deliberate decision to ensure programmatic relevance, since the WHO and most National TB Programmes in high-burden TB settings do not require a positive test of TB infection before initiating preventive therapy in children who have been exposed to a person living with infectious drug-susceptible TB [31].

#### Choice of intervention regimen

We considered a wide range of anti-TB drugs and drug combinations for the intervention arm of the trial, including first-line TB drugs, third generation fluoroquinolones, ethionamide, *para*-aminosalicylic acid (PAS), cycloserine, linezolid and clofazimine, and the novel drugs, bedaquiline and delamanid. We discounted drugs if: (1) resistance was likely to be present to that drug in MDR strains (the first-line drugs) [32, 33]; (2) the drug is likely to be poorly tolerated (ethionamide and PAS); (3) the drug is associated with frequent or serious AEs (cycloserine, linezolid, clofazimine); (4) the drug is only weakly effective in killing *M. tuberculosis* (cycloserine, clofazimine, PAS); or (5) appropriate formulations are unavailable or pharmacokinetic parameters are not well understood (delamanid and bedaquiline).

We therefore decided to use a third-generation fluoroquinolone. These drugs have good efficacy against *M. tuberculosis* in vitro and are a core component of MDR-TB disease treatment regimens in both adults and children. Historically, clinicians had been hesitant to use fluoroquinolones in children following early animal research demonstrating cartilage damage in juvenile beagles [34]. However, a significant body of evidence has now demonstrated that drugs of this class are safe in children, even for long-term use [9, 35–38]. Although moxifloxacin has good efficacy against metabolically active mycobacteria, levofloxacin may have better activity against metabolically inactive mycobacteria [39]. A mouse model which evaluated a number of novel TB infection treatment regimens in a latent infection model found that levofloxacin, moxifloxacin and isoniazid had similar efficacy against drug-susceptible strains of *M. tuberculosis.* Moxifloxacin is poorly tolerated in its current formulation due to its bitter taste and there are challenges in taste masking the active ingredient [40]. In addition, the large milligram size of the tablet (400 mg) makes dosing challenging in children. Levofloxacin, in contrast, has a low tablet milligram dose, is licensed for children, has been widely used to treat paediatric MDR-TB disease and other bacterial infections, has known pharmacokinetic parameters when used at once-daily dosing [41], does not interact with antiretroviral therapy drugs and appears to have low toxicity at currently used dosages [42].

Some limited rationale exists for the additional use of isoniazid in a preventive therapy regimen, as it would be efficacious in preventing disease if the child had been exposed to a person with drug-susceptible TB in addition to the identified MDR-TB case. As young children are likely to be highly concordant with the identified source case, we anticipate few children acquiring drug-susceptible organisms. Isoniazid may also provide some efficacy against MDR strains with *inhA* promoter region mutations (typically conferring low-level resistance) [43]. Globally, however, isoniazid resistance is more commonly caused by *katG* gene mutations [44], in which isoniazid is less likely to be effective. For these reasons we elected not to include isoniazid in the intervention regimen. Paediatric pharmacokinetic and safety data for delamanid are becoming increasingly available and the WHO now recommends delamanid for the treatment of MDR-TB disease in children aged as young as six years, but not yet to the youngest children, where treatment of infection is most needed [45]. We plan to adapt the trial design to include delamanid to treat child contacts of fluoroquinolone-resistant MDR-TB, in an observational cohort, once pharmacokinetic data and formulations become available for the youngest children, dependent on additional funding.

In designing our intervention, we also considered that a simple regimen with one drug would likely be safer and would facilitate easier adherence for children. Although concerns have been raised that the use of a single drug could lead to the acquisition of secondary resistance in individuals who develop TB disease, this has not been shown to occur with the use of isoniazid as a single agent for TB preventive therapy in adult and child contacts of drug-susceptible TB [21, 46]. We therefore decided to use levofloxacin alone.

#### Choice of control regimen

As outlined above, isoniazid may be active against *M. tuberculosis* with *inhA* promoter region mutations, as well as susceptible strains from exposures other than the identified index case. For these reasons, the PHOENIx randomised controlled trial (A5300/IMPAACT2003), evaluating MDR-TB infection treatment with delamanid, chose isoniazid for their control arm. However, as also stated above, we anticipate high concordance between index case and child contact (with few children infected with drug-susceptible strains), as well as globally limited utility of isoniazid to treat MDR strains (due to the preponderance of *katG* gene mutations worldwide). In addition, the inclusion of isoniazid would increase the (albeit low) risk of harm that could arise through the use of a potentially hepatotoxic drug. Given the lack of evidence for the efficacy for isoniazid to treat MDR-TB infection and the lack of guidance on this topic, the protocol team, after broad scientific and ethical consideration, determined that it would be most appropriate to use no active drug in the control arm. This represents current WHO guidance [31].

#### Blinding

We considered using an open-label design. However, the primary trial endpoint, incident TB, although standardised to as great a degree as possible, remains, to some extent, subjective. Many children who develop incident TB during the trial will be diagnosed clinically (i.e. not bacteriologically confirmed). The study team felt that with an open-label design there may be bias in the ascertainment of the endpoint. Children known not to be receiving any medication may be followed more closely and investigated more intensively than children known to be on treatment. In addition, there would be potential for bias in the ascertainment and reporting of AEs, with families/caregivers potentially more likely to report AEs if they knew their child was taking an active treatment. We therefore decided blinding and use of placebo would support unbiased assessment of endpoints and toxicity.

#### Clustering

As we planned to identify and treat children in their households, we felt that all children in the same household should be randomised to the same trial arm. Randomisation by household allows for ease of drug administration and protection from bias through accidental or deliberate switching of tablets (levofloxacin/placebo) between child household contacts. The statistical implications of the clustering are accounted for in the sample size estimation and analysis plan.

### Context

South Africa had an estimated TB incidence of 834 cases per 100,000 in 2015 with 3.5% of new cases and 7.1% of previously treated TB cases having either MDR-TB or rifampicin-resistant-TB [3]. The national HIV antenatal prevalence was 29.7% in 2013 [47]; in 2015, of all TB patients with known HIV status, 57% were estimated to be HIV-infected [3]. The trial is being conducted at three sites in South Africa, all of which have extensive research experience in TB trials: (1) Desmond Tutu TB Centre, Stellenbosch University, Cape Town; (2) Perinatal HIV Research Unit, Wits Health Consortium, Klerksdorp; and (3) Wits Reproductive Health and HIV Institute, Wits RHI Shandukani Research Centre, Johannesburg. Trial management, statistical design and analysis, and clinical event management is provided by the Medical Research Council Clinical Trials Unit (MRC CTU) at University College London. The trial began recruitment in September 2017 and recruitment is planned over 18–24 months. All children receive 24 weeks of therapy and are followed for 72 weeks after treatment.

### Trial endpoints

The primary endpoint is incident TB disease (bacteriologically confirmed or clinically diagnosed) or TB death by 48 weeks following randomisation. Incident TB and cause of death are adjudicated by an independent Endpoint Review Committee blinded to treatment allocation, based on available clinical, radiological, microbiological and molecular data using standard case definitions (see Table 1). Secondary endpoints are: (1) all-cause mortality; (b) AEs ≥ grade 3 (possibly or likely associated with drug treatment) during 24 weeks of treatment; (3) percentage of levofloxacin or levofloxacin-placebo doses ingested and retained over 24 weeks of treatment; (4) TB disease over 96 weeks; and (5) incidence of levofloxacin-resistant TB disease.

**Table 1 Tab1:** Clinical and radiological/laboratory criteria required to make a diagnosis of confirmed, probable or possible TB in child TB contacts aged < 5 years of age. Developed in collaboration with the trial teams from V-QUIN and PHOENIx

Clinical (A)	Radiological/laboratory (B)
• Cough or cervical neck mass (≥2 × 2 cm) for > 2 weeks despite a course of antibiotics • Fever or lethargy for > 1 week despite a course of antibiotics • Documented failure to thrive, i.e. flattening of weight curve crossing centiles, documented weight loss, e.g. > 5%, moderate or severe malnutrition (Weight-for-height Z score < − 2) in relation to previous measures • Classic gibbus suggestive of spinal TB • Depressed level of consciousness, new onset seizures or focal neurological signs suggestive of TB meningitis	• AFBs or caseating granulomas on microscopy (not confirmed by culture or Xpert to be TB) • CXR suggestive of TB (concurrence between two blinded CXR reviewers, with conflicts resolved by third reviewer) despite a course of antibiotics • CSF suggestive of TB (white cell count 10-500 cells per µl with a lymphocyte predominance, protein > 1 g/dL, glucose < 2.2 mmol/L) • Pleural aspirate or ascitic tap with WBC counts, protein, and glucose levels suggestive of TB, consider ADA • CT brain suggestive of CNS TB

• Confirmed TB: positive *M. tuberculosis* + at least one of either A or B

• Positive *M. tuberculosis:* (adapted from Graham et al. [57]): at least one positive culture (with confirmed *M. tuberculosis* speciation) or one positive WHO-endorsed NAAT (e.g. XpertMTB/RIF assay) from respiratory samples (expectorated/induced sputum or gastric aspirate) or other samples such as fine needle aspiration biopsy or other fluid or tissue samples

• Probable TB: at least one of A and at least one of B

• Possible TB: at least one of A or B (but not both) and a decision to treat

• Not TB: the absence of clinical, radiological or laboratory evidence that meets any of the above criteria

• TB infection: immunological evidence of infection with *M. tuberculosis* (TST/IGRA) plus classification as ‘Not TB’.

• Indeterminate/unclassifiable TB status: documented results of the diagnostic evaluation (suspicious symptoms, chest radiograph, laboratory tests) are insufficient for the Endpoint Review Panel to reach determination

• Death: mortality will be classified as death from any cause. TB deaths will be verified using available data (including death certificate, post mortem, hospital and other clinical information or other as available). The Endpoint Review Committee will review and determine the cause of death, if there are any deaths, in all children participating in the trial. Death occurring during a TB episode will be classified as TB death, unless there is clear evidence that the death is unrelated (e.g. motor vehicle accident)

*TB* tuberculosis, *AFBs* acid-fast bacilli, *CXR* chest radiograph, *ADA* adenosine deaminase, *CNS* central nervous system, *CSF* cerebrospinal fluid, *CT* computed tomography, *IGRA* interferon-gamma release assay, *TST* tuberculin skin test, *WBC* white blood count, *WHO* World Health Organization, *NAAT* nucleic acid amplification test

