### Adverse events

Safety assessments are conducted at each visit during the 24 weeks on treatment and include evaluation of symptoms, signs and laboratory investigations. At every study visit (and at unscheduled visits) a symptom checklist prompts for symptoms relating to possible drug toxicities. All symptomatic patients are evaluated by the study doctor and discussed with the site Principal Investigator. Safety laboratory investigations are performed at baseline and at 8, 16 and 24 weeks and are also performed at unscheduled visits if clinically indicated. AEs (clinical and laboratory) are graded using the 2017 Division of AIDS toxicity grading scale [52]. All AEs are recorded in the child’s notes and reported to the MRC CTU and ethics committees as required within agreed timescales. There are no known drug–drug interactions between levofloxacin and antiretroviral drugs used to treat children living with HIV [42] and a recent evaluation of long-term levofloxacin use in children with MDR-TB found no evidence of cardiotoxicity or QTc prolongation [53].

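### The only adverse-event endpoint counts grade ≥3 events judged drug-related; a comparison of all grade ≥3 events by arm should be added beside it

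*Protocol article*

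**What the plan says.** Under Trial endpoints, the adverse-event item among the secondary endpoints covers events of grade 3 or worse that are "possibly or likely associated with drug treatment) during 24 weeks of treatment". One other listed endpoint bears on harm without needing attribution: the list opens "Secondary endpoints are: (1) all-cause mortality". No item counts all grade ≥3 events.

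The Adverse events section describes wider data capture than this endpoint uses. It states that "AEs (clinical and laboratory) are graded using the 2017 Division of AIDS toxicity grading scale" and that "All AEs are recorded in the child’s notes and reported to the MRC CTU". On who looks at the child, it says only that "All symptomatic patients are evaluated by the study doctor and discussed with the site Principal Investigator". It does not say who decides whether an event is drug-related.

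The Blinding section gives the reason for the placebo: "We therefore decided blinding and use of placebo would support unbiased assessment of endpoints and toxicity". The Discussion makes the expected move into policy depend on levofloxacin being safe and tolerated as well as effective.

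**The concern.** The trial pays for a placebo arm and blinding partly so that toxicity can be compared fairly. With those in place, the difference between arms shows what the drug causes. A child-level causality filter is a further, subjective step that the comparison does not need. Its weak point is a drug-caused event that is not recognised as one: it is judged unrelated and never enters the endpoint.

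The children are enrolled free of TB disease and whatever their infection-test result, so tolerance for unrecognised harm is low. If endpoint (b) alone carried the safety conclusion, that conclusion would be only as good as the attribution, and the article gives nothing from which to judge how good that is. An independent blinded committee adjudicates incident TB and cause of death; no such step is described for the relatedness of adverse events.

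**Working it through.** **Calibration on the plan's own figure.** The Statistical considerations section gives 7% v 3.5%, two-sided 5%, 80% power, intra-class correlation 0.1, two children per household and 10% loss.

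- Pooled-variance formula for two proportions, no continuity correction: 637 children per arm.
- Design effect: 1 + (2 − 1) × 0.1 = 1.1.
- Total: 637 × 1.1 / 0.9 × 2 = 1557, against 1556 stated.
- Power at 778 × 0.9 / 1.1 = 636.5 effective children per arm: 80.0%.

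The formula therefore matches the plan's. The plan's figure concerns efficacy only; the article gives no rate or power for adverse events.

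**Safety comparison: inputs.**

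- Effective children per arm: 778 / 1.1 = 707. This carries over the efficacy intra-class correlation and takes off no losses.
- Assumed grade ≥3 risk over 24 weeks: 4% on placebo and 7% on levofloxacin, that is, a 4% background in both arms plus 3 points caused by the drug.
- *s*: assumed share of drug-caused events judged related. *f*: assumed share of background events judged related.

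**Formulae.** Attributed risk on placebo = 0.04*f*. Attributed risk on levofloxacin = 0.04*f* + 0.03*s*. With the two risks p₁ and p₂, their mean p̄ and n per arm,

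power = Φ{ [ |p₂ − p₁|√n − 1.96√(2p̄(1 − p̄)) ] / √(p₁(1 − p₁) + p₂(1 − p₂)) }.

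For all events: p̄ = 0.055, and (0.798 − 0.632) / 0.322 = 0.516, so power = Φ(0.516) = 69.7%.

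| *s* | *f* | Placebo | Levofloxacin | Power |
|---|---|---|---|---|
| all events | all events | 4.0% | 7.0% | 70% |
| 75% | 10% | 0.40% | 2.65% | 93% |
| 75% | 20% | 0.80% | 3.05% | 87% |
| 60% | 20% | 0.80% | 2.60% | 75% |
| 75% | 50% | 2.00% | 4.25% | 68% |
| 50% | 20% | 0.80% | 2.30% | 63% |
| 50% | 25% | 1.00% | 2.50% | 58% |
| 50% | 50% | 2.00% | 3.50% | 41% |
| 25% | 10% | 0.40% | 1.15% | 36% |
| 30% | 30% | 1.20% | 2.10% | 26% |

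Rows with *s* = *f* are uninformative attribution: events are removed without regard to cause, and power falls. Where attribution separates drug-caused from background events well, the filter removes noise and power rises.

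**A second assumed scenario.** With a 5% background and a 2-point excess, all events give 35%. Attributed events give 72% (*s* = 75%, *f* = 10%), 36% (75%, 50%), 30% (50%, 25%), 20% (50%, 50%) and 19% (25%, 10%). Again the direction depends on *s* and *f*.

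**The case against.** The strongest case for the plan is that limiting the endpoint to drug-related severe events is a recognised choice, trading some missed events for less background noise, and that the table shows the trade can pay. That stands. A reader might infer from the filter that the trial has less chance of seeing harm; the document does not support this, because it gives neither the background rate nor the attribution accuracy that would fix the direction.

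A reader might also infer that the randomised, blinded comparison has been thrown away. It has not. Relatedness is judged under blinding in both arms, so the attributed comparison is itself randomised and blinded, and all adverse events remain on record. Nor is endpoint (b) the only safeguard: all-cause mortality is a separate endpoint, safety laboratory tests are scheduled on treatment, and the Independent Data Monitoring Committee sees unblinded data.

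Two further inferences go beyond the text. The article does not say that site investigators assign relatedness. Nothing in it shows that unexpected events will be called unrelated; the threshold of a possible association is low, and a blinded clinician in doubt may well use it.

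Finally, the full protocol and any analysis plan are not shown, and tables of all severe events by arm are commonly left to them. That limits the point to the endpoint as written. It does not remove it, because the article itself states which events enter its one adverse-event endpoint.

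**Conclusion.** The concern holds as a point about endpoint definition. The one listed adverse-event endpoint depends on a causality judgement of unknown accuracy that this design does not require, and drug-caused events not recognised as such fall outside it.

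Its size cannot be fixed from the document. With an assumed 4% v 7% and 707 effective children per arm, power is 70% for all events and about 26% to 93% for attributed events. That range covers the scenarios shown and is not a bound. It rests on assumed event rates, assumed values of *s* and *f*, and the efficacy intra-class correlation applied to adverse events.

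The uncertainty argues for reporting both comparisons, not for replacing one with the other: the all-event result does not depend on attribution, and the attributed result may be the sharper one if attribution is good. This is a worthwhile, inexpensive improvement to a secondary endpoint. It is neither an internal contradiction nor a numerical error, and it does not touch the primary analysis.

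**What to change.** Extend secondary endpoint (b) with a between-arm comparison of children with any grade ≥3 adverse event from randomisation to the week-24 visit, regardless of attribution, using a method that allows for household clustering. Keep the present attributed-event comparison, report the two side by side, and state that any conclusion on safety will be drawn from both. If the full protocol or analysis plan already contains the all-event comparison, it is enough to bring the endpoint list into line with it.

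The cost is a little more analysis, and the reported severe-event rates will look higher in both arms because background illness is counted. No new visits, tests, data or sample size are needed, since adverse events are already graded and recorded.
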